### C. Participant Payment

Participants will receive \$20 for completion of Screening visit T0. If an individual attempts a confirmatory blood draw at T0, but a blood sample is not able to be drawn (e.g., phlebotomist is unable to access an appropriate vein), the participant may return a second day for no more than three attempts for which they will be paid \$20. If a blood sample is not able to be drawn, the participant would still receive the full payment but is not eligible to participate if initial lab work cannot be completed. Participants who are eligible to receive treatment will be asked to complete the ACASI survey at time T1 and will receive \$20. Participants deemed ineligible at time T1 will be provided with their results, appropriate referrals and \$10. Participants will receive \$20 for attending the brief 4 week check-in visit, then \$30, \$30, \$40 and \$50, respectively, for completing the procedures at the four follow-up visits.

Enrolled and randomized participants can be paid \$20 for successfully referring another eligible participant. In order to receive payment, the referred individual must be fully eligible and randomized; the referring participant will receive payment after the referred participant completes T1.

### D. Provision of Syringes, Harm Reduction Kits and naloxone

Study staff will distribute sterile syringes to and collect used syringes from PWIDs in keeping with community standards. Syringes will be provided by our harm reduction partners and will not be purchased with federal funds. We will prepare and distribute harm reduction kits (e.g. condoms and sterile tourniquets, cottons, cookers and waters), and information on local treatment resources to interested participants. As in the UG3 phase, study staff will receive training on how to use and distribute naloxone. The states of Vermont and New Hampshire have agreed to supply study staff with naloxone for distribution.

### E. Analysis Plan.

**Primary outcomes** will be the proportion of PWID who initiate DAA treatment, achieve sustained virologic response at 12-weeks post-treatment (SVR12), and report no syringe sharing in the prior 30 days at follow-up. We hypothesize that, compared with EUC, mobile tele-HCV care will be associated with:

H1: higher rates of DAA treatment initiation,

H2: higher rates of sustained virological response 12-weeks post treatment (SVR12 or cure), and

H3: lower rates of syringe sharing behavior among rural HCV-infected PWIDs

Secondary outcomes will include HBV and HAV vaccination series completion rates, initiation of MOUD and ED visits, as well as health-related quality of life (HRQOL) and substance use.

**Preliminary Analyses:** Initial data analysis will describe the distribution of all outcomes by study group. Continuous measures will be reported using means, standard deviations, medians and percentiles. Categorical measures will be reported using frequencies and percentages. Rather than testing for baseline covariate imbalance, stratified analyses will be conducted for baseline covariates that are known to be strongly associated with outcomes, as well as those that show imbalance on inspection.

**Primary outcome analyses.** We will apply ICH-E9 guidelines for statistical analysis and the CONSORT statement for reporting of findings. Since Aims 1 and 2 examine the effectiveness of the intervention by comparing proportions in the two study groups, we will apply the same statistical approach. For the univariable approach, study groups will be compared using Pearson's chi-square or Fisher's exact test. Stratification and adjustment for relevant baseline covariables will be accomplished with logistic regression. In

these models, study group and other categorical measures will be represented with indicator variables. Continuous explanatory variables will be evaluated to verify linearity of their logit and, if not, they will be rescaled. Model fit will be examined and final results will be expressed as odds ratios and adjusted proportions each with 95% confidence intervals. Significance testing will be conducted at a critical level of 5%.

**Heterogeneity of Treatment Effect.** Heterogeneity of treatment effect will be examined by both pre-planned sub-group analyses and more exploratory approaches. Pre-specified sub-groups will be defined based on a) demographic factors, such as age, race/ethnicity, income (if available), marital status, and b) opioid use characteristics, such as duration of use. We will follow best practice and base tests of statistical significance on regression-based interaction terms (e.g., interaction of sub-group status with study group) so that the full sample size is used to maximize power. Further, to address the loss of power with sub-group analyses, we will explore for clinical relevance any planned interaction achieving  $p \leq 0.20$ . More exploratory approaches will be used to classify participants according to the likelihood of intervention using regression-based approaches, potentially yielding a layer of insight not available from the more restrictive pre-defined sub-group analyses.

**Missing Data.** Missing data may arise from subject dropout, non-compliance, or item nonresponse. Several approaches to assess the impact will be undertaken. In general, we will use all available data regardless of whether a patient has a complete record. Participants with missing data will be compared to those without to check for differences. We will explore missing data to evaluate the presence of patterns. Secondly, making the assumption that the data are missing at random (MAR), multiple imputation methods will be used to generate data for the missing values based upon the distribution of available data (using SAS PROC MI or Stata's MI IMPUTE), and results of multiple sets combined into a summary measure with appropriate statistical tests (SAS PROC MIANALYZE or Stata's MI ESTIMATE). Results from each strategy will be compared to analyses using the complete data.

**Sample size.** Sample size and power estimates are based on a comparison of two proportions (PASS v.15). From the UG3 phase of the study, we enrolled 589 participants, of which approximately 344 tested positive for HCV. Among these with supplementation, we will recruit at least 220 (about 64%) for the UH3 phase. Because mobile vans are expensive to implement, we believe that, at a minimum, a moderate effect size should be required to be meaningful from the public health, clinical and policy perspectives.

For treatment initiation, we expect 50% or fewer participants in the EUC to initiate treatment, and the MTC intervention to improve initiation to at least 70%. Thus, 220 individuals randomized equally to two groups would provide 86% power to detect a 20% absolute difference between study groups for a test of difference in proportions at  $P < .05$ . This difference is equivalent to an odds ratio of 2.33, or a medium effect size.

For sustained viral response at 12 weeks post-treatment (SVR12), an intent-to-treat approach would include all participants randomized. We expect the success rates to be lower than for the "as-treated" approach, since attrition may occur both at initiation of therapy, as well as completion of therapy. Thus a sample of 110 participants per group would provide about 80% power to detect difference in the proportion of treatment success of 30% in the EUC and 48.5% in the MTC group. This difference is equivalent to an odds ratio of 2.12, which is equivalent to a medium effect size (approximate Cohen's  $d = 0.42$ ). Because the lower treatment initiation rate in the EUC group will favor the MTC group, we also present an as-treated sample size calculation. We expect about 55 patients (i.e., 50% of 110) in the EUC group and at least 77 patients (70% of 110) in the MTC to initiate treatment. Again, we expect the MTC intervention to overcome substantial obstacles to achieving SVR12. As such, a difference in the proportion of participants achieving SVR12 at least as large as 25% is expected. Thus a sample of 132 participants (55 in usual care and 77 in intervention), would provide about 82% power to detect a difference between the MTC intervention and EUC groups of 25% absolute difference (i.e., 65% vs. 40%) for a test of difference in proportions at a critical level of 5%. This difference is equivalent to an odds ratio of 2.79, which is about a medium effect size (equivalent to Cohen's  $d$  of 0.56)

For injection sharing behavior, our UG3 survey found that 77% of HCV-infected PWIDs shared *any* equipment in the 30 days prior, and 66% shared syringes. Using an ITT approach, a sample of 110 participants per group would provide at least 80% power to detect a 19% or greater reduction in sharing behaviors for

either measure (i.e., 77% vs. 58% for sharing any equipment, and 66% vs. 47% for sharing syringes only) for a two-sided test in the difference in proportions at a critical level of 5%. The 19-point difference for these outcomes yields an OR of about 2.4, which equates to a medium effect size (approximate Cohen's  $d = 0.48$ ).

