### 1. Inclusion Criteria:

- a. Current or past history of drug injection;
- b. Health insurance that will cover HCV medications (study staff will work with those who are eligible but have not signed up for insurance once consented and enrolled in study)
- c. Lives in one of the 10 study counties in NH and VT, and plans to remain in the study region for the next 12 months;
- d. Age 18 years or older;
- e. Speaks English;
- f. Capacity to voluntarily provide informed consent;
- g. Will accept randomized assignment, and participate in follow-up over 12 months;
- h. Will provide releases to access community medical records;
- i. Will provide names and contact information of at least 3 persons for re-contact purposes;
- j. Not previously treated for HCV;
- k. Not pregnant or trying to conceive;
- l. HCV antibody positive on point-of-care rapid test.

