**Randomization (also at Visit T1).** Individuals whose specimens are positive for HCV viremia and negative for HBsAg will be randomly assigned 1:1 to Enhanced Usual Care (EUC) or Mobile Tele-HCV Care. Based on feedback gathered during Community Engagement Studios conducted with UG3 study participants, it was determined that randomization should occur in as transparent a manner as possible to address any potential participant concerns around bias or personal discrimination. During Visit T1, eligible participants will sit down with research staff and will witness the randomization process, which will be done using a computer program that utilizes block randomization in real time. Computerized block randomization will ensure balance by study site, gender, and current (last 30 days) drug injection.

[figure not shown]

**Figure 1. Recruitment and Study flow.** Staff on the van will also offer Narcan nasal inhalers, cottons, sterile water, clean cookers, rubber tourniquets, condoms and sterile syringes (provided by harm reduction partners purchased from non-federal sources) at every visit. If resources permit, services would be provided to anyone who approaches the van, but at a minimum, to all who have initiated study procedures (eligible and ineligible).

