## 5. Data Collection

**a. Audio Computer Assisted Survey Instrument (ACASI).** Drs. [name] and [name] led development of a harmonized quantitative survey with partners in all eight Rural Opioid Initiative (UG3) sites in 2017-2018. Of the eight UG3 sites, five are currently using the ACASI version developed at the Tufts University School of Medicine. The other three sites are using the harmonized survey in CAPI platforms (RedCap, Qualtrics). Survey domains that are included in all harmonized instruments include: sociodemographics; substance use; injection behavior (including syringe sharing), sex risk behavior, overdose prevalence, substance use treatment, and sexual-mediated risk behaviors; self-reported infectious disease and health status; access to harm reduction (e.g., SSPs, naloxone), MOUD, and health care services; knowledge, attitudes, and experience with such services; geospatial locations of community assets, risks, and place of residence; mobile phone and texting practices and experiences; criminal justice involvement and egocentric and sociometric social networks.

As in the UG3 phase, we will develop and deploy a modified version of our existing ACASI harmonized across the ROI sites to assess participants at baseline and follow-up. We will incorporate domains focused on HCV screening, confirmatory testing, and treatment experiences; telehealth exposure, experience, and satisfaction; additional measures focused on enhanced syringe access, syringe sharing and injection-mediated risks; and experience and satisfaction with our mobile harm reduction and tele-care van. Final core survey questions will be harmonized with those decided upon by the UH3 National Executive Steering Committee. Drs. [name] and [name] are ready and willing to assist the Data Coordinating Center (DCC) with harmonization of measures and instruments across all funded UH3 sites. Where applicable, we will use common data elements such as those from the National Library of Medicine.

**b. Follow-up Interval.** All participants will have one brief check-in visit approximately 4 weeks after treatment initiation to order more medication or consult with physician (via telemedicine or over the phone, as

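### The primary analyses are unranked and covariates may be picked on observed imbalance, so the randomisation factors can be left out; for H3 this could cost power

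*Protocol*

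**What the plan says.** **Randomisation** (Protocol, section IV.B.3). Participants "will be randomly assigned 1:1 to Enhanced Usual Care (EUC) or Mobile Tele-HCV Care", and "Computerized block randomization will ensure balance by study site, gender, and current (last 30 days) drug injection". Current injection varies between participants because the inclusion criteria admit "Current or past history of drug injection".

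**Primary outcome analyses** (Protocol, section IV.E). Under what it labels the univariable approach, "study groups will be compared using Pearson's chi-square or Fisher's exact test". The next sentence adds: "Stratification and adjustment for relevant baseline covariables will be accomplished with logistic regression". Final results are to be odds ratios and adjusted proportions, tested at 5%. The section does not say which approach decides H1 to H3, and it does not list the covariables.

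**Preliminary analyses** (same section). Baseline imbalance will not be tested formally. Instead, stratified analyses are planned for covariates already known to predict the outcome strongly, "as well as those that show imbalance on inspection".

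**Sample size** (same section). Every power figure rests on an unstratified comparison of two proportions.

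**Data available** (Protocol, section IV.B.5). The ACASI survey, given at baseline and follow-up, covers "injection behavior (including syringe sharing").

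**The concern.** Blocking on a factor that predicts the outcome removes chance imbalance in that factor between the arms. A test that ignores the factor still counts this imbalance as noise. Its standard error is then too large, its true type I error falls below 5%, and power is lost.

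This matters mainly for H3. Someone who has not injected in the last 30 days can be expected to share syringes rarely, so current injection should predict 30-day sharing strongly.

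The inspection rule adds two problems. The adjustment set then depends on the observed data. And because site, gender and current injection are balanced by blocking, they will seldom look imbalanced, so this trigger tends to miss the factors with the best claim to be in the model. With two unranked approaches as well, the protocol leaves open which result counts.

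**Working it through.** **1. The plan's own figure.** Inputs from the sample-size text: 66% v 47% sharing syringes, 110 per arm, two-sided 5%. With pooled SE = √(2·0.565·0.435/110) = 0.0668 and actual SD = √((0.66·0.34 + 0.47·0.53)/110) = 0.0656:

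Power = Φ((0.19 − 1.96·0.0668)/0.0656) = 81.6%, which agrees with the stated figure of at least 80%. The H1 figure (86.2%; stated 86%) and the H2 intention-to-treat figure (80.7%; stated about 80%) also reproduce.

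**2. Assumptions for the check.** The protocol does not give the share of current injectors, q, or the sharing rate among the rest. I apply 66% v 47% to current injectors and assume 5% in both arms among non-current injectors.

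**3. Type I error of the unstratified test.** Under the null, with allocation balanced within injection strata:

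- Variance the test assumes: T = p(1 − p), where p = 0.66q + 0.05(1 − q).
- Variance that applies: W = 0.66·0.34·q + 0.05·0.95·(1 − q).
- Type I error = 2[1 − Φ(1.96/√(W/T))].

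For q = 0.8: p = 0.538, T = 0.2486, W = 0.1890, W/T = 0.7605, and 1.96/0.872 = 2.247, giving 2.5%. The same steps give 3.5% at q = 0.9 and 1.8% at q = 0.7. Simulating the trial gives about 3.7%, 2.7% and 2.1% at q = 0.9, 0.8 and 0.7. Slightly higher values are expected, because unfinished blocks leave some imbalance.

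**4. Power for H3.** For q = 0.8 the overall rates are 53.8% v 38.6%, a difference of 0.152. The actual SD is √((0.1890 + 0.2088)/110) = 0.0601.

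- Unstratified: SE = √(2·0.462·0.538/110) = 0.0672. Power = Φ((0.152 − 1.96·0.0672)/0.0601) = 63%.
- Stratified: SE = √(2·(0.8·0.565·0.435 + 0.2·0.05·0.95)/110) = 0.0612. Power = Φ((0.152 − 1.96·0.0612)/0.0601) = 70%.

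| Non-current injectors | Type I error, unstratified (simulated) | Power, unstratified | Power, stratified |
|---|---|---|---|
| 0% | 5% | 82% | 82% |
| 10% | 3.7% | 73% | 76% |
| 20% | 2.7% | 63% | 70% |
| 30% | 2.1% | 52% | 63% |

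**5. Sensitivity.** These are simulations with blocks of four within site × gender × injection strata (four sites and 40% in one gender assumed). The stratified analysis is a Cochran-Mantel-Haenszel (CMH) test over those strata.

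- Non-current injectors never share, 20% non-current: power 63% v 72%.
- Non-current injectors share 15% v 10%, 20% non-current: type I error 3.5% v 5.1%, power 68% v 73%.
- 66% v 47% taken as the overall rates, with non-current injectors never sharing, 20% non-current: power 85% v 94%. The unstratified test then passes 80% but still gives up power.

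In the H3 settings with 0% to 50% non-current injectors, the stratified test's type I error stayed between about 4.5% and 5.7%.

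**6. H1 and H2.** With an assumed 15-point difference in outcome by injection status and 30% non-current, power is 86.0% v 86.0% for H1 and 81.3% v 81.8% for H2. Type I error is 4.7% to 4.9% unstratified and 4.8% to 5.2% stratified.

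**7. Baseline sharing in H3.** One simulation assumed that baseline sharers are 40 points more likely to share later. Adding baseline sharing raised power from 69% to 76% at 20% non-current, and from 81% to 87% with none. The size of this gain depends on the assumed association.

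**The case against.** The protocol does not make the unstratified test the primary comparison. It labels the test univariable, provides logistic adjustment in the next sentence, and reports adjusted proportions. The other limb of the covariate rule, covariates already known to predict the outcome strongly, does not depend on trial data and could take in current injection and baseline sharing for H3. Choosing the confirmatory model and its covariates is commonly left to the SAP, which is not at hand. All of this stands, and it limits the point.

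A reader might infer that the trial's primary test is the wrong one, that power is wasted across the primary outcomes, or that H3 carries too many false positives. The documents support none of these. The two approaches are unranked, H1 and H2 change by less than one point of power, and the error for H3 is on the conservative side.

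Much of the fall in H3 power is also dilution by people who rarely share, which no analysis recovers. At 20% non-current, power falls from 82% to 63%, and stratification restores it only to 70%.

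The inspection rule is different. It is not a detail left for later: the protocol states it, and it is poorly chosen for a design that blocks on known factors.

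**Conclusion.** The point holds in a limited form. The protocol leaves two primary approaches unranked, does not tie the analysis to its randomisation factors, and states a covariate trigger that is data-dependent and tends to miss those factors.

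If the unstratified test decides H3, the cost attributable to that choice is about 3, 7 and 11 points of power at 10%, 20% and 30% non-current injectors (76 − 73, 70 − 63, 63 − 52). It is nil if all participants currently inject. These sizes rest on an assumed share of non-current injectors and an assumed 5% sharing rate among them; milder assumptions shrink the gap. This is a free improvement, not an error that threatens the validity of the trial.

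**What to change.** In the Analysis Plan, or the SAP if it governs:

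- Make the study-group term in a logistic model, or a CMH test, the confirmatory test for H1 to H3, with site, gender and current injection as pre-specified covariates.
- Add baseline 30-day syringe sharing as a covariate for H3.
- Keep the unadjusted chi-square or Fisher test as supportive.
- Delete "as well as those that show imbalance on inspection" as a trigger for adjustment.

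The cost is wording only. The randomisation factors are known at allocation, and the baseline survey covers syringe sharing. The number of sites is not given, so add a rule, fixed before the data are seen, for pooling small sites.

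### The heterogeneity plan groups age, income and duration of use before the interaction test; testing them as continuous would usually give more power at no cost in data

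*Protocol*

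**What the plan says.** The relevant text is in the Protocol, section IV.E Analysis Plan, under Heterogeneity of Treatment Effect.

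- The moderators: "Pre-specified sub-groups will be defined based on a) demographic factors, such as age, race/ethnicity, income (if available), marital status", and "opioid use characteristics, such as duration of use". Age, income and duration of use are naturally continuous or ordered; race/ethnicity and marital status are categorical.
- The test: the plan will "base tests of statistical significance on regression-based interaction terms (e.g., interaction of sub-group status with study group"). With the reason attached, the example reads "interaction of sub-group status with study group) so that the full sample size is used to maximize power".
- The plan knows that power is short: "to address the loss of power with sub-group analyses, we will explore for clinical relevance any planned interaction achieving" p ≤ 0.20. It also adds exploratory regression approaches, because it regards the pre-defined sub-groups as restrictive.

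The paragraph on primary outcome analyses, just before it, handles continuous variables differently in the logistic models used for stratification and adjustment: "Continuous explanatory variables will be evaluated to verify linearity of their logit and, if not, they will be rescaled". Nothing carries that rule over to the interaction tests.

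**The concern.** A sub-group indicator treats everyone on one side of a cut as alike. If the benefit of mobile care changes gradually with age or with years of use, the differences within each group carry information about that trend, and the grouped test discards it. A single model on the full sample does not bring it back.

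Interaction tests already have little power in a trial sized for main effects, so this avoidable loss falls where it can least be afforded. Real dependence of the effect on age or duration would be missed more often than necessary, and the answer would depend on where the cuts fall. The plan already has the better tool, a continuous term with a linearity check, but does not say that it applies here.

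**Working it through.** **Inputs from the protocol.** 220 randomised, 110 per group; treatment initiation 50% (EUC) vs 70% (MTC); 5% level, taken as two-sided; exploration screen p ≤ 0.20. No power figure is given for any interaction test.

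**Assumptions, because the protocol gives no figure.** The number of groups, the cut-points, the moderator's distribution, and an interaction that is linear on the logit scale.

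**Step 1. The plan's own figure.** Two-proportion test, pooled variance:

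z = [0.20·√110 − 1.96·√(2·0.6·0.4)] / √(0.5·0.5 + 0.7·0.3) = (2.098 − 1.358)/0.678 = 1.09, so power is 86.2%. The stated 86% reproduces.

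With half the sample (55 per group), as in a separate test within one of two equal sub-groups, z = (1.483 − 1.358)/0.678 = 0.18 and power is 57%. The preference for one full-sample model is therefore sound.

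**Step 2. Information kept after grouping.** For a standardised moderator X cut into groups with shares p_j, the share of the linear information kept is Σ p_j·(E[X | group j])².

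| Distribution and grouping | Kept | Lost |
|---|---|---|
| Normal, median split (2/π) | 63.7% | 36.3% |
| Normal, 30/70 | 57.6% | 42.4% |
| Normal, 25/75 | 53.9% | 46.1% |
| Normal, 20/80 | 49.0% | 51.0% |
| Normal, tertiles | 79.3% | 20.7% |
| Normal, quartiles | 86.1% | 13.9% |
| Normal, quintiles | 89.7% | 10.3% |
| Uniform, 2 / 3 / 5 equal groups | 75% / 89% / 96% | 25% / 11% / 4% |
| Exponential (skewed), median split ((ln 2)²) | 48.0% | 52.0% |

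For the normal median split, 220 × 0.637 ≈ 140 effective participants.

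**Step 3. What this does to power (normal moderator).** A continuous test with 80% power at two-sided 5% has non-centrality (1.960 + 0.842)² = 7.85. Multiply by the share kept and use the degrees of freedom of the grouped test:

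- Median split, 1 df: 7.85 × 0.637 = 5.00, power 61%.
- Tertiles, 2 df: 7.85 × 0.793 = 6.23, power 60%.
- Quartiles, 3 df: 7.85 × 0.861 = 6.76, power 57%.

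More groups keep more information, but the extra degrees of freedom use up the gain. A 1 df trend across tertiles would do better: √6.23 − 1.96 = 0.54, power about 70%.

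**Step 4. Simulation check.** 3,000 logistic data sets per scenario, 110 per group, normal moderator with no effect under EUC, initiation 50% vs 70% at its mean, Wald test of the interaction. Monte Carlo standard error is at most √(0.25/3000) = 0.9 points.

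| Interaction log-OR per SD (OR) | p < 0.05: continuous vs median split | p ≤ 0.20: continuous vs median split |
|---|---|---|
| 0 | 5.0% vs 4.8% | 20.8% vs 20.2% |
| 0.60 (1.82) | 52.5% vs 36.3% | 77.6% vs 63.8% |
| 0.85 (2.34) | 80.4% vs 60.7% | 94.1% vs 83.1% |

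Both tests hold their level. The p ≤ 0.20 screen narrows the gap, but 11 to 14 points remain. These are strong interactions: at 0.85 per SD the MTC odds ratio runs from exp(0.847 − 0.85) = 1.0 at one SD below the mean to exp(0.847 + 0.85) = 5.5 at one SD above.

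**The case against.** The strongest reply is that the protocol does not fix the choice. It commits to regression-based interaction terms and brings in sub-group status only as an example. A continuous term is not ruled out, and the coding of moderators is commonly left to the statistical analysis plan, which is not shown. This stands in part. The absence of cut-points is no defect, and the point should not be put as one. But the paragraph says that sub-groups will be defined on these variables, and its example points the same way, so the plain reading is grouping.

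Three stronger readings are tempting and not supported:

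- A reader might infer that the power claim is false. It is tied to using the full sample in one model, and against separate sub-group tests it is right (86% vs 57% in Step 1). It says nothing about grouped against continuous coding.
- A reader might infer that the two paragraphs contradict each other. They do not: one concerns stratification and adjustment of the main comparison, the other effect modification. Adjusting for continuous age and showing effects by age group can sit together.
- A reader might put the loss at a third. That needs a median split of a normal moderator with a linear interaction, and the protocol states none of these.

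It is also fair to say that the plan acknowledges the power loss and softens it with the 0.20 screen and exploratory models, and that grouping need not lose power if the effect is a threshold near the cut.

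**Conclusion.** The point holds as a minor one. Followed as plainly written, the plan groups naturally continuous moderators before testing them, and for a roughly linear interaction that costs power which the full-sample model does not restore. The information loss is about 10% to about 50% over the normal-moderator groupings considered, 36% for a median split, about half for a skewed moderator split at its median, and less for an evenly spread one. In power terms, a normal moderator's 80% falls to about 60% with a median split or a 2 df tertile test.

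These figures rest on assumed groupings, distributions and a linear interaction; the protocol supplies none of them. No primary test, sample size or error rate is affected.

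**What to change.** In the heterogeneity paragraph of section IV.E:

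1. State that age, duration of use and income (if recorded as an amount) are tested as continuous moderator by study group interactions. Use the linearity check already planned for the primary models, or a restricted cubic spline, for shape.
2. Keep sub-groups for displaying results, and keep sub-group status tests for truly categorical moderators (race/ethnicity, marital status).
3. Limit the power claim to the comparison with separate tests within sub-groups.

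The cost is wording only; no new data are needed where the variables are recorded as continuous. The downside is an assumed functional form, which the linearity check or spline addresses. The change is best made before outcomes are known, so that neither coding nor cut-points can follow the results.
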